# A randomized, active-controlled, parallel, open-label, multicenter, phase 4 study to compare the efficacy and safety of pregabalin sustained release tablet and pregabalin immediate release capsule in type II diabetic patients with peripheral neuropathic pain

**DOI:** 10.1097/MD.0000000000033701

**Published:** 2023-04-28

**Keywords:** analgesics, diabetic neuropathies, medication adherence, pregabalin

## Abstract

**Background::**

Diabetic peripheral polyneuropathy is the most common chronic complication of type 2 diabetes. Neuropathic pain is challenging to manage, and various drugs are required to control it, decreasing treatment adherence. Pregabalin, a ligand that binds to alpha-2-delta subunits of the presynaptic calcium channel, has been approved by the Food and Drug Administration for the treatment of diabetic neuropathic pain. In this study, we will compare the efficacy, safety, treatment satisfaction, and compliance between pregabalin sustained-release (SR) tablets and pregabalin immediate-release (IR) capsules in type 2 diabetic patients with peripheral neuropathic pain.

**Methods::**

This study is a randomized, active-controlled, parallel, open-label, multicenter, phase 4 clinical trial (trial registration NCT05624853). Type 2 diabetic patients with glycosylated hemoglobin below 10% and peripheral neuropathic pain who have been taking pregabalin 150 mg/d or more for more than 4 weeks will be randomly assigned to pregabalin SR tablet (150 mg once a day, n = 65) or pregabalin IR capsule (75 mg twice a day, n = 65) therapy for 8 weeks. The primary outcome will be the efficacy of SR pregabalin after 8 weeks of treatment, which will be assessed by visual analog scale measurements. The secondary outcomes will include changes in several parameters, such as quality of life, treatment satisfaction, quality of sleep, and drug compliance.

**Discussion::**

In thus study, we aim to demonstrate that pregabalin SR tablets are associated with better compliance and satisfaction compared with pregabalin IR capsules, despite similar efficacy.

## 1. Introduction

Diabetic neuropathy is the most prevalent chronic complication of type 1 and 2 diabetes mellitus; over 50% of people living with diabetes will develop this condition throughout their lifetime.^[1–3]^ Among the broad spectrum of diabetic neuropathies, diabetic peripheral neuropathy (DPN) is the most common type. Neuropathic pain, a major problem in DPN, remains difficult to manage despite previous efforts to develop therapeutic approaches. This results in several problems such as sleep disturbances, reduced quality of life, and socioeconomic consequences (e.g., depressed mood, reduced ability to work or perform daily activities, and increased health care costs).^[4–6]^ Painful DPN can eventually lead to a loss of sensation and lower limb amputation, which can increase mortality; therefore, early diagnosis and treatment are critical.^[7]^

Pregabalin, a ligand of the alpha-2-delta subunits of the presynaptic neuronal calcium channel, reduces pain by inhibiting the release of neurotransmitters involved in pain sensation.^[2,8]^ This drug was approved by the U.S. Food and Drug Administration in 2004. It is indicated for the treatment of neuropathic pain associated with DPN, spinal cord injury, and postherpetic neuralgia,^[8,9]^ and is generally considered a first-line treatment for painful DPN in most guidelines.^[10]^ There is evidence that the efficacy of pregabalin against painful DPN is dose-dependent.^[1,11–13]^ It can be administered twice or occasionally 3 times daily, and most patients require 300 mg/d or more for symptomatic relief. Recently, an extended-release formulation of pregabalin was approved by the U.S. Food and Drug Administration for the treatment of painful DPN and postherpetic neuralgia.^[14]^ Additionally, a new, once-daily, sustained-released (SR) pregabalin formulation (YHD1119 tablets; Yuhan Corporation, Seoul, Republic of Korea; now marketed as Yuhan Pregabalin SR Tab.) was shown to be effective and safe in a randomized, non-inferiority phase 3 study conducted in Korea.^[15]^ However, there is limited real-world data comparing the efficacy, safety, and medication adherence between immediate-release (IR) and SR formulations of pregabalin. Therefore, in this study, we aim to evaluate the efficacy, safety, and medication adherence of pregabalin SR compared with those of pregabalin IR.

## 2. Methods

### 2.1. Study design

This is a randomized, active-controlled, parallel, open-label, multicenter, phase 4, non-inferiority study conducted at 8 sites using either pregabalin SR tablets or pregabalin IR capsules. This study has been registered at Clinical Trial.gov (identifier NCT05624853).

### 2.2. Study ethics

The study will be conducted in accordance with the Declaration of Helsinki and Ethical Guidelines for Clinical Research, and the institutional review boards at each site will review the protocol and other relevant documents prior to study initiation. All participants will be required to provide written informed consent before enrollment.

### 2.3. Study population

Patients with type 2 diabetes taking pregabalin IR 150 mg/d for at least 4 weeks before screening will be recruited. The inclusion and exclusion criteria are provided below:

•Inclusion criteria:
1.Patients capable of providing written informed consent2.Male or female patients between 19 and 75 years old3.Patients with type 2 diabetes mellitus (T2DM) and glycosylated hemoglobin (HbA1c) ≤ 10%4.Patients who experience moderate to severe pain associated with DPN (visual analogue scale [VAS] score ≥ 30 at screening)5.Patients with stable concomitant treatment for underlying disease6.For women of childbearing potential:
a.Negative serum or urine pregnancy test at the screening visitb.Willing to use appropriate contraception during the study

•Exclusion criteria:
1.Patients who are hypersensitive to the study drug or any of its components2.Patients who are taking anticonvulsants3.Patients who are experiencing non-DPN-related pain4.Patients with other types of neuropathies not related to DPN5.Patients with abnormal clinical research laboratory results at screening, defined as:
a.Estimated glomerular filtration rate < 30 mL/min/1.73 m^2^b.More than 3 times the upper normal limits of alanine transaminase or aspartate transaminase
6.Patients with active liver disease7.Patients with a history of alcohol or drug abuse8.Patients determined by the investigator to be unsuitable for participation because of severe depression, uncontrolled mood disorder, or behavioral changes9.Pregnant or lactating women10.Patients participating in another clinical trial within 30 days of screening11.Patients deemed ineligible for this clinical trial by the investigator

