### 2.4. Randomization and treatment

Eligible participants who have VAS scores ≥ 30 at screening will be randomized to receive either IR or SR pregabalin in a 1:1 ratio by a computer-generated sequence without stratification. Pregabalin will be administered open-label, and patients will receive the assigned medication for 8 weeks. The study group will receive SR pregabalin tablets of 150 mg once a day starting in the evening, and the control group will receive IR pregabalin capsules of 75 mg twice a day until the morning of the last day of the study (Fig. 1). No dose adjustments will be made during the intervention period. If intolerable pain occurs during the trial, patients will be allowed to use rescue medication using acetaminophen at a maximum dose of 2000 mg/d. From 4 weeks before randomization until the end of the study, patients may use analgesics other than pregabalin as long as the same formulation and doses are maintained.

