### 2.6. Statistical analysis

Based on previous studies of IR pregabalin compared with placebo in patients with DPN,^[20]^ the sample size will be calculated as follows: with a margin of non-inferiority of 9.2 mm, 80% statistical power, and a significance level of 2.5% for 1-sided testing, assuming no difference in VAS scores between the 2 groups and a standard deviation of 0.6, approximately 65 subjects per treatment group will be required to demonstrate non-inferiority. Assuming a 20% dropout rate, 130 participants will be recruited (65 per group).

Full Analysis Set will be used as the main analysis group to evaluate efficacy while Per-Protocol Set will be used as a subanalysis set; Safety Set will be analyzed for safety data.

Differences in VAS scores in each group after 8 weeks of treatment compared with baseline will be described statistically (number of subjects, mean, standard deviation, median, minimum, and maximum) and analyzed by analysis of covariance corrected for baseline as a covariate. SR pregabalin will be considered non-inferior to IR pregabalin if the lower bound of the 95% confidence interval for the least squares mean difference between the treatment groups is greater than the prespecified non-inferiority margin of 9.2 mm. The secondary endpoints will be analyzed using either analysis of covariance or Pearson’s chi-square test, depending on the characteristics of the variables. In addition, demographics, baseline characteristics, treatment compliance, and safety endpoints will be summarized using descriptive statistics. Treatment adherence will be calculated by dividing the number of tablets taken by the number of tablets scheduled for administration and then multiplying by 100. The data will be analyzed using IBM SPSS Statistics for Windows, Version 20 (IBM, Armonk, NY).

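### Because entry requires residual pain on IR pregabalin, a non-inferiority result would not by itself establish similar efficacy

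*Protocol article*

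**What the plan says.** **Entry.** Section 2.3 states "Patients with type 2 diabetes taking pregabalin IR 150 mg/d for at least 4 weeks before screening will be recruited" and lists as an inclusion criterion "Patients who experience moderate to severe pain associated with DPN (visual analogue scale [VAS] score ≥ 30 at screening". Section 2.4 repeats the VAS threshold as a condition for randomization. The abstract (Methods) describes entry differently: patients "who have been taking pregabalin 150 mg/d or more for more than 4 weeks", with no formulation named.

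**Comparator.** Section 2.4 says "the control group will receive IR pregabalin capsules of 75 mg twice a day until the morning of the last day of the study", which is 150 mg/d, and rules out dose changes during the 8 weeks.

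**Dose and effect.** The Introduction reports evidence of a dose-dependent effect in painful DPN and adds that "most patients require 300 mg/d or more for symptomatic relief".

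**Margin and sample size.** Section 2.6 introduces the calculation with "Based on previous studies of IR pregabalin compared with placebo in patients with DPN" and uses a 9.2 mm margin, one-sided 2.5% significance and 80% power.

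**Claim.** The abstract (Methods) says "The primary outcome will be the efficacy of SR pregabalin after 8 weeks of treatment". The abstract (Discussion) aims to show that "pregabalin SR tablets are associated with better compliance and satisfaction compared with pregabalin IR capsules, despite similar efficacy". Section 3 closes by saying the trial will confirm real-world efficacy and safety of SR.

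**The concern.** A two-arm non-inferiority trial shows that the new product works only indirectly. The active control must have an effect over placebo, in the patients enrolled and at the dose used, that is larger than the margin. Ruling out a loss as large as the margin then implies that some effect remains.

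Three features weaken that link here. Patients qualify by still having pain on the control drug, so those well controlled on it are excluded. The control continues at a daily dose that the Introduction describes as too low for symptomatic relief in most patients. The placebo-controlled evidence cited for the calculation comes with no effect size, dose or account of prior treatment, and nothing in the article links it to patients selected in this way. The article describes no placebo arm, washout or requirement of earlier response that would fill the gap.

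Change from baseline does not fill it either. Under section 2.3, baseline is measured on pregabalin at the study dose, so a fall within an arm does not measure what the drug does.

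What is at stake is the wording of the conclusion. A pass could be reported as similar efficacy when it shows only that switching did not worsen pain by more than the margin.

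**Working it through.** **1. The plan's own figure.** Inputs from section 2.6: margin 9.2 mm, SD 0.6 (no unit), true difference 0, one-sided 2.5%, power 80%.

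n per group = 2 × (1.960 + 0.842)² × (0.6 / 9.2)² = 2 × 7.85 × 0.00425 = 0.07, which rounds up to 1. The stated 65 per group is not reproduced. This is a separate defect, but it means the document gives no usable SD and one must be assumed.

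**2. Assumed standard error.** I take the value that yields the stated power at the stated margin:

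SE = 9.2 / (1.960 + 0.842) = 3.28 mm.

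This corresponds to an SD of 18.7 mm if 65 per group are evaluable (18.7 × √(2/65) = 3.28), or 16.7 mm if 52 are (65 × 0.8 = 52; 16.7 × √(2/52) = 3.28).

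**3. Chance that an inert product passes.** Let d be the true effect of IR 150 mg/d over placebo in the enrolled patients. The documents do not give it. A product with no effect is then d mm worse than IR. Reading the decision rule as excluding a worsening of 9.2 mm or more,

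P(declare non-inferior) = Φ((9.2 − d) / SE − 1.96).

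Example at d = 5 mm: (9.2 − 5) / 3.28 − 1.96 = 1.28 − 1.96 = −0.68, and Φ(−0.68) = 0.25.

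| d (mm) | P, SE 3.28 mm |
|---|---|
| 0 | 80% |
| 2 | 59% |
| 3 | 47% |
| 5 | 25% |
| 7 | 10% |
| 9.2 | 2.5% |

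**4. Sensitivity to the SD.** With SD 25 mm and 52 per group, SE = 25 × √(2/52) = 4.90 mm.

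| d (mm) | P, SE 3.28 mm | P, SE 4.90 mm |
|---|---|---|
| 0 | 80% | 47% |
| 2.3 | 56% | 29% |
| 4.6 | 29% | 15% |
| 6.9 | 10% | 7% |
| 9.2 | 2.5% | 2.5% |

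The size depends on the SD; the direction does not. For any SE, the probability is 2.5% at d = 9.2 mm, higher below it and lower above it.

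**5. Entry dose.** Under section 2.3 everyone enters on 150 mg/d and the control arm continues unchanged. Under the abstract, some could enter on more and be moved to 150 mg/d at randomization. In that case baseline would not be at the study dose, and the control arm would not be a plain continuation. The two statements describe different populations.

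**The case against.** A reader might infer that the design cannot show similar efficacy at all, or has no assay sensitivity. The documents do not support that. A VAS of 30 or more on treatment is residual pain, not proof of non-response: pain before pregabalin is not recorded, and a partial responder can still score above 30. The Introduction says most patients need more than 150 mg/d, not that 150 mg/d does nothing. If IR still gives these patients at least 9.2 mm, replacing it with something ineffective would be detected at the nominal error rate. This stands.

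A reader might also infer that regression to the mean biases the comparison towards success. It does not: selection on VAS acts on both randomized arms alike, and section 2.6 decides on the between-group difference adjusted for baseline. The baseline point concerns only how within-arm change is interpreted, and no section says that such change will be read as efficacy.

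An inert SR product is a remote scenario. SR carries the same drug at the same daily dose, and the Introduction and section 3 cite a randomized phase 3 trial in which SR was non-inferior to IR. This also stands. However, the article does not give that trial's dose or its patients' prior treatment, so it does not validate this margin in this population.

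The probabilities are hypothetical, since d is unknown and the SE is solved backwards from the stated power. The 80% at d = 0 is simply the planned power: if IR does nothing, an inert product really is no worse.

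Finally, the derivation of the margin may sit in the full protocol, so its absence from an article is no fault. The efficacy wording, however, is in the article itself.

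**Conclusion.** The concern holds in a limited form. Entry selects for residual pain on the control, the control continues at a dose whose adequacy the article itself questions, and the IR-versus-placebo effect behind the calculation cannot be assumed in these patients. A non-inferiority result would therefore not by itself establish similar efficacy or the efficacy of SR.

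The size depends on two unknowns: the IR effect in the enrolled patients and the SD. At an IR effect of 5 mm and an assumed SE of 3.28 mm, an inert product would pass about 25% of the time. At 4.6 mm the figure is 29%, or 15% with SD 25 mm and 52 per group. At 9.2 mm or more it is 2.5% or less.

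The absolute reading, that efficacy cannot be shown, goes too far. What is missing is support for the inference, not proof that it fails. This should be fixed, but it does not invalidate the randomized comparison, which remains a sound answer to the switching question.

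**What to change.** 1. In the abstract (Methods and Discussion) and section 3, restate the objective and conclusion along these lines: switching from IR to SR at the same daily dose does not worsen pain by more than the margin, compared with continuing IR, in patients with residual pain on IR.
2. State that within-arm change from an on-treatment baseline will not be read as evidence of efficacy.
3. Claim preserved efficacy only if the IR-versus-placebo effect at the trial's own daily dose is shown, beside the margin, to exceed it.
4. Reconcile the abstract and section 2.3 on the entry dose and formulation. Which version is intended is for the sponsor to say.

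These are changes of wording and justification. They need no extra patients, visits or analyses. The price is a narrower claim.

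I would not add a subset analysis by recalled relief on IR. Recall cannot separate drug effect from placebo response or natural fluctuation. If half the patients reported relief, the SE would rise to 3.28 × √2 = 4.64 mm and power would fall to Φ(9.2 / 4.64 − 1.96), about 51%.

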### 2.4. Randomization and treatment

Eligible participants who have VAS scores ≥ 30 at screening will be randomized to receive either IR or SR pregabalin in a 1:1 ratio by a computer-generated sequence without stratification. Pregabalin will be administered open-label, and patients will receive the assigned medication for 8 weeks. The study group will receive SR pregabalin tablets of 150 mg once a day starting in the evening, and the control group will receive IR pregabalin capsules of 75 mg twice a day until the morning of the last day of the study (Fig. 1). No dose adjustments will be made during the intervention period. If intolerable pain occurs during the trial, patients will be allowed to use rescue medication using acetaminophen at a maximum dose of 2000 mg/d. From 4 weeks before randomization until the end of the study, patients may use analgesics other than pregabalin as long as the same formulation and doses are maintained.

**Figure 1. F1:**
[figure not shown]
Study design.

The investigator or clinical research coordinator will provide participants with instructions on how to take medication correctly. We will assess medication adherence by determining the amount of study drug not administered at the end of study visit (visit 3). At the final visit, all study drug (leftover tablets and packs) will be collected, and the investigator will check the quantity of the study drug. The number of days between the last visit and end of the treatment period will also be recorded. The percentage of medication adherence will be calculated by dividing the number of pills taken by the number of pills scheduled for administration during the treatment period. If a subject loses their study drug, they must receive a medical examination to confirm the loss, which will then be recorded in the source document and case report form.

### 2.5. Study endpoints and assessments

#### 2.5.1. Primary endpoint.

The primary endpoint of this study will be changes in the VAS score, defined as the difference in VAS scores from the start of the study and after 8 weeks of treatment.

#### 2.5.2. Secondary endpoints.

The secondary endpoints will include the following:

1.Changes from baseline after 8 weeks of treatment in:
a.Quality of life (EQ-5D-3L)^[16]^b.Treatment satisfaction of clinical subjects (Patient Global Impression of Change)c.Treatment satisfaction of the investigator (Clinician Global Impression of Change)d.Sleep disturbance (Daily Sleep Interference Scale)^[17]^e.Medication adherence index (Morisky medication adherence scale 8-item version)^[18]^
2.Frequency, dose, and duration of rescue medication use after administration of the study drug

#### 2.5.3. Safety and clinical laboratory tests.

Height and weight will be recorded at the first visit. Smoking history, alcohol consumption, and vital signs will be assessed at each visit. Clinical laboratory tests will include complete blood count and measurement of aspartate aminotransferase, alanine aminotransferase, alkaline phosphatase, creatinine kinase, uric acid, total bilirubin, total protein, albumin, sodium, potassium, chloride, phosphorus, blood urea nitrogen, serum creatinine, and HbA1c levels. Biomarkers will be measured from a blood sample from each patient at each visit, with the exception of HbA1c. The estimated glomerular filtration rate will be calculated using the creatinine-based Modification of Diet in Renal Disease equation.^[19]^ The number of subjects, incidence rate and number of occurrences of treatment-emergent adverse events, adverse drug reactions, and serious adverse events after pregabalin administration will be recorded and analyzed.

### 2.6. Statistical analysis

Based on previous studies of IR pregabalin compared with placebo in patients with DPN,^[20]^ the sample size will be calculated as follows: with a margin of non-inferiority of 9.2 mm, 80% statistical power, and a significance level of 2.5% for 1-sided testing, assuming no difference in VAS scores between the 2 groups and a standard deviation of 0.6, approximately 65 subjects per treatment group will be required to demonstrate non-inferiority. Assuming a 20% dropout rate, 130 participants will be recruited (65 per group).

Full Analysis Set will be used as the main analysis group to evaluate efficacy while Per-Protocol Set will be used as a subanalysis set; Safety Set will be analyzed for safety data.

Differences in VAS scores in each group after 8 weeks of treatment compared with baseline will be described statistically (number of subjects, mean, standard deviation, median, minimum, and maximum) and analyzed by analysis of covariance corrected for baseline as a covariate. SR pregabalin will be considered non-inferior to IR pregabalin if the lower bound of the 95% confidence interval for the least squares mean difference between the treatment groups is greater than the prespecified non-inferiority margin of 9.2 mm. The secondary endpoints will be analyzed using either analysis of covariance or Pearson’s chi-square test, depending on the characteristics of the variables. In addition, demographics, baseline characteristics, treatment compliance, and safety endpoints will be summarized using descriptive statistics. Treatment adherence will be calculated by dividing the number of tablets taken by the number of tablets scheduled for administration and then multiplying by 100. The data will be analyzed using IBM SPSS Statistics for Windows, Version 20 (IBM, Armonk, NY).

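### The printed standard deviation of 0.6 gives 1 patient per group, not 65, so the sample size and 80% power have no valid stated basis

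*Protocol article*

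**What the plan says.** All the planning inputs stand in the first paragraph of section 2.6 of the protocol article. The margin, power and alpha are given as "with a margin of non-inferiority of 9.2 mm, 80% statistical power, and a significance level of 2.5% for 1-sided testing". The expected treatment effect is set by "assuming no difference in VAS scores between the 2 groups". The variability and the result follow: "a standard deviation of 0.6, approximately 65 subjects per treatment group will be required to demonstrate non-inferiority". The next sentence reads "Assuming a 20% dropout rate, 130 participants will be recruited (65 per group", so 65 per group also appears as the number recruited after allowing for dropout.

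Section 2.4 fixes allocation "in a 1:1 ratio by a computer-generated sequence without stratification". Section 2.3 requires a "visual analogue scale [VAS] score ≥ 30 at screening", which together with a margin in mm places the outcome on a millimetre-type scale. The SD carries no unit, and no other SD appears anywhere in the article. The assumptions are attributed to a cited earlier comparison of IR pregabalin with placebo.

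**The concern.** The ratio of margin to SD drives a non-inferiority sample size. A 9.2 mm margin against an SD of 0.6 is more than 15 standard deviations (9.2 / 0.6 = 15.3), and no trial with such a ratio would need 65 patients per group. An SD of 0.6 mm is also hard to credit for change in pain on a scale where entry requires at least 30.

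Once margin, alpha, power and expected difference are set, the SD is the one remaining input to this calculation, so the 80% power claim stands or falls with it. If the trial fails to exclude the margin, readers will want to know whether SR is really worse or the trial was too small to tell. The sample-size statement should help them judge that, and as printed it cannot.

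**Working it through.** **Inputs** (protocol article, sections 2.4 and 2.6): margin M = 9.2 mm; true difference 0; one-sided alpha 0.025 (z = 1.960); power 80% (z = 0.842); SD = 0.6; allocation 1:1; dropout 20%.

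**Formula**, for two means with no true difference:

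n per group = 2 × (1.960 + 0.842)² × SD² / M² = 15.70 × SD² / 84.64

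**The plan's figure, inputs as printed.** 15.70 × 0.36 / 84.64 = 0.067, so 1 per group. That is a normal-approximation value. A two-sample t-test needs at least 2 per group, and at that size power already exceeds 99.9%. The stated 65 is not reproduced.

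**Other readings of 0.6**

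| Reading | n per group | After 20% dropout (n / 0.8) |
|---|---|---|
| SD 0.6 mm | 1 | 2 |
| SD 0.6 cm = 6 mm (or margin 0.92 with SD 0.6) | 7 | 9 |
| 0.6 as the margin in SD units (SD = 9.2 / 0.6 = 15.3 mm) | 44 | 55 |
| SD 60 mm | 668 | 835 |

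Reading 0.6 as a standard error from 52 to 100 patients implies an SD of about 4.3 to 6.0 mm (0.6 × √52 to 0.6 × √100), again far too small. With one-sided alpha at 0.0125 or 0.05, or power at 90%, the result stays at 1 per group for an SD of 0.6 and at 6 to 11 for 6 mm. None of these gives 65, or the 52 that remain after 20% dropout.

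**Working backwards.** SD = M × √(n/2) / 2.802:

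- 65 analysed: 9.2 × √32.5 / 2.802 = 18.7 mm, which is 31 times 0.6.
- 52 analysed (65 × 0.8): 9.2 × √26 / 2.802 = 16.7 mm, which is 28 times 0.6.

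Conversely, an SD of 0.6 with 65 per group corresponds to a margin of 0.6 × 2.802 / √32.5 = 0.295 on the same scale.

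**Power at the planned size.** One-sided 2.5%, margin 9.2 mm, no true difference, noncentral t, no allowance for baseline adjustment. The SDs of 20 to 25 mm are an assumed range and do not come from the article.

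| SD of change (mm) | 52 analysed per group | 65 analysed per group |
|---|---|---|
| 16.7 | 80% | 88% |
| 18.7 | 70% | 79% |
| 20 | 64% | 74% |
| 22 | 56% | 66% |
| 25 | 46% | 55% |

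The normal approximation gives values within about one percentage point of these.

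**The case against.** The best defence is that 0.6 is a reporting slip and the underlying calculation was sound. An SD of about 16.7 mm gives 52 per group, and 52 / 0.8 is exactly 65, so a coherent derivation of the recruited number exists. That is plausible, but it is inference. The text calls 65 both the number required and the number recruited after dropout, so a reader cannot tell whether 16.7 or 18.7 mm was used. The source study is cited, but its figures are not given.

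Three further points limit the consequences:

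- The main analysis uses the Full Analysis Set, so some patients who drop out may still be analysed. The number could lie anywhere from 52 to 65 per group, and the column for 52 is the less favourable end.
- The primary analysis is a covariance analysis adjusted for baseline, so the correlation between baseline and outcome also affects power and could recover some of it.
- The planning SD enters neither that analysis nor the confidence-interval rule, so the eventual result does not depend on the misprint.

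All three stand, and they rule out a claim that the trial is underpowered. None of them makes the printed inputs agree with the printed sample size.

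**Conclusion.** The concern holds. As printed, the inputs give 1 per group against a stated 65, and no reading of the unit or formula variant tried reaches 65 or 52. The stated size implies an SD of 16.7 to 18.7 mm, some 28 to 31 times the figure given. This conclusion uses only the article's own numbers and the standard two-sample formula.

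What is established is that the 80% power has no valid stated basis, not that 130 patients are too few. How far power might fall depends on an SD that the article does not supply. Over the assumed range of 20 to 25 mm it is 46% to 64% with 52 analysed per group and 55% to 74% with 65, before any gain from baseline adjustment.

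**What to change.** In section 2.6, replace 0.6 with the SD of the VAS change, in mm, that was actually used, and name its source. Rerun the formula and restate the required number per group, saying clearly whether 65 is before or after the 20% dropout allowance. If 65 must be analysed, 65 / 0.8 gives 82 per group to recruit. If 65 is the recruited number, 52 are expected to be analysed.

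Then give the power at the planned 130 patients in a short table, at SDs of 16.7, 18.7, 20 and 25 mm, for 52 and ideally also 65 analysed per group.

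The cost is a corrected sentence and a recalculation. The correction itself adds no patients, but the restated power may be less favourable than 80%, and whether 130 is adequate can be judged only once the true planning SD is stated.

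### Section 2.6 gives 65 per group both as the number required for 80% power and as the number recruited after a 20% dropout allowance; one of these figures, or the stated power, is wrong as written

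*Protocol article*

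**What the plan says.** The sample size is set out in the first paragraph of section 2.6 (Statistical analysis) of the protocol article. Its inputs are:

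- margin: "with a margin of non-inferiority of 9.2 mm"
- power: "80% statistical power"
- error rate: "a significance level of 2.5% for 1-sided testing"
- true difference: "assuming no difference in VAS scores between the 2 groups"
- variability: "a standard deviation of 0.6", with no unit

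From these the article concludes that "approximately 65 subjects per treatment group will be required to demonstrate non-inferiority". The next sentence deals with losses: "Assuming a 20% dropout rate, 130 participants will be recruited (65 per group").

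The Methods part of the abstract confirms 65 as the number allocated to each arm, for example "pregabalin SR tablet (150 mg once a day, n = 65"). No smaller number of evaluable patients appears anywhere in the article. The main efficacy analysis uses the Full Analysis Set, with the Per-Protocol Set as a subanalysis.

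**The concern.** A dropout allowance converts the number needed for the analysis into a larger number to recruit. Here the same number stands on both sides of the conversion. Either the allowance was never applied, or it was applied and the result was then described as the requirement. The two sentences cannot both be right.

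This matters because the trial is a non-inferiority study whose primary conclusion relies on this calculation. If the allowance is missing, the power after the planned loss is below 80%, and a failure to show non-inferiority could reflect too few patients rather than a real difference between the formulations. If the allowance is there, the trial is sized as intended, but a reader cannot tell. In both cases the stated power cannot be verified from the text.

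**Working it through.** **Inputs from section 2.6:** margin 9.2 mm, SD 0.6 (no unit), true difference 0, one-sided alpha 0.025, power 80%, dropout 20%, 65 per group. Section 2.4 gives 1:1 allocation.

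**Step 1. Reproduce the plan's figure.** For two means with true difference 0,

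n per group = 2 × SD² × (z₀.₉₇₅ + z₀.₈₀)² / margin², with 1.960 + 0.842 = 2.802 and 2.802² ≈ 7.85.

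With the printed inputs: 2 × 0.36 × 7.85 / 84.64 = 0.07, so 1 per group. The plan's 65 is not reproduced. Other readings of the units do not recover it:

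| Margin | SD | n per group |
|---|---|---|
| 9.2 | 0.6 | 1 |
| 0.92 (cm) | 0.6 | 7 |
| 9.2 | 6 | 7 |
| 9.2 | 60 | 668 |

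One-sided 5% gives 1, 6, 6 and 526 in the same order, and 90% power gives 1, 9, 9 and 894. None gives 65 or 52, so the printed SD cannot show whether 65 is the number before or after inflation.

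**Step 2. Dropout arithmetic.** Recruited = evaluable / (1 − 0.20).

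- If 65 is the evaluable number: 65/0.8 = 81.25, so 82 per group, 164 in total.
- If 65 is the recruited number: 65 × 0.8 = 52 evaluable, and 52/0.8 = 65 exactly.

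**Step 3. SD that each reading would need.** This is back-solved and is an assumption, not a figure in the article: SD = margin / (2.802 × √(2/n)).

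- n = 65: 9.2 / (2.802 × 0.1754) = 18.72 mm (18.58 mm with the t distribution).
- n = 52: 9.2 / (2.802 × 0.1961) = 16.74 mm (16.59 mm with the t distribution).

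**Step 4. Power on each reading.** Power = Φ(margin / (SD × √(2/n)) − 1.960).

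If 65 is the evaluable requirement (SD 18.72 mm):

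- n = 52: 9.2 / (18.72 × 0.1961) = 2.506; Φ(0.546) = 70.7% (70.6% with the t distribution).
- n = 58: 9.2 / (18.72 × 0.1857) = 2.647; Φ(0.687) ≈ 75%.
- n = 60: 9.2 / (18.72 × 0.1826) = 2.692; Φ(0.732) ≈ 77%.

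On this reading, the risk of missing true non-inferiority rises from 20% to about 29% at 52 evaluable.

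If 65 is already inflated (SD 16.74 mm), power at 52 evaluable is 80.0% and nothing is lost.

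With the printed SD of 0.6, power at 52 would be essentially 100%, which again shows that 0.6 cannot be the value behind the calculation.

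**The case against.** A reader might infer that the allowance was simply forgotten and that the trial has 71% power instead of 80%. The article does not support that as a fact, for three reasons.

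First, 52/0.8 is exactly 65. That is what one would see if 52 were required, 65 were recruited, and the condensed text attached the requirement to the wrong number. Power at 52 evaluable would then be 80% as claimed. This objection stands: the article does not decide between the readings.

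Second, the 71% does not follow from the printed inputs. It needs an SD of about 18.7 mm, obtained by supposing that 65 evaluable give exactly 80%. This also stands, and it means that 71% is a conditional figure.

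Third, 52 evaluable supposes that every dropout disappears from the primary analysis. The main set is the Full Analysis Set, which may keep some early leavers; its definition is not in the article, and its absence is no fault of a condensed report. So 52 is the low end for the main analysis. On the literal reading, however, any loss from 65 takes power below 80%, and the plan's own allowance treats dropout as reducing the usable sample.

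None of the three removes the contradiction. Both numbers are printed, in consecutive sentences, so this is not a detail left to a fuller document.

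**Conclusion.** The point holds as an internal contradiction: section 2.6 uses 65 per group both as the requirement for 80% power and as the recruitment figure under 20% dropout. One of those figures, or the stated power, is wrong as written.

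The consequence depends on which reading is true:

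- If 65 is the evaluable requirement, recruitment falls short by 17 per group (82 − 65). Power is about 71% at 52 evaluable and about 75% at 58, given an assumed SD of about 18.7 mm.
- If 65 is already inflated, there is no loss of power and the error is one of wording.

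Confidence is high for the contradiction. An unconditional loss of power is not established. The unusable SD of 0.6 in the same sentence is part of the problem, because it prevents anyone from settling the question by recalculation.

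**What to change.** Correct the text of section 2.6 without enrolling more patients:

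1. State which number 65 is. Either say that 52 evaluable per group are required and 65 per group are recruited, or keep 65 as the requirement, keep 130 recruited, and restate the power expected at 20% dropout (about 71% under the condition given above).
2. In the same edit, replace the SD of 0.6 with the value actually used, giving its unit and source.
3. Recompute the requirement or the power from that SD. The back-solved values of 16.7 and 18.7 mm serve only to show the size of the discrepancy and should not be entered as planning assumptions.

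The cost is a text correction and one recalculation. The drawback is that the stated power may become less favourable.
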